## Method/design

### Primary and secondary objectives

The primary objective is to test if the incidence of revision surgery (primary endpoint) is lower in patients ≤65 years with an initially displaced FNF treated with the DLBP in comparison to treatment with DHS. Secondary objectives are to determine the incidence of AVN, non-union, implant related complications, non-implant related complications and elective removal after fixation with the DLBP or DHS. Also, we compare operating time, functional outcome and cost-effectiveness of DLBP and the DHS.

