#### Secondary outcome parameters

*Incidence of avascular necrosis*: AVN is defined as hip pain in combination with radiographical signs for AVN as described by Steinberg [19]. According to the Steinberg classification AVN is present from stage 2 and upward. AVN will be assessed by the treating surgeon. As is customary in the Netherlands, all radiographs are also assessed by a radiologist.

*Incidence of non-union*: there is no consensus in the literature regarding to the definition of (non-)union [20]. Our definition of non-union is based on the Radiographic Union Score for Hip (RUSH) [21]. Non-union is a visible fracture line on the radiograph, absence of cortical bridging or bridging trabeculae over the fracture site in combination with persisting pain in the hip and the inability to bear weight at least 9 months post-operative or sooner if revision surgery was performed because it was no longer expected that fracture healing would occur. Non-union will be assessed by the treating surgeon.

*Incidence of implant related complications:* an implant related complication is defined as breakage or cut-out of the plate or screws, inadequate expansion/malfunction of the anchors or any malfunction of the implant which may or may not lead to revision surgery. Implant related failure will be monitored during 1 year of follow up.

*Post-operative complications*: post-operative complication is defined as any unanticipated event other than the above mentioned, for which operative treatment or medical treatment is required, e.g. wound infection, bleeding or pneumonia. Every complication occurring during the hospital stay of the patient will be recorded.

*Rate of elective implant removal after union*: Elective implant removal after union will be recorded during 1 year of follow up after surgery. Reasons for elective removal will be described.

*Functional outcome:* patient-reported post-surgical function will be scored using the validated Dutch version of the International Hip Outcome Tool (iHOT-12NL) [22]. The iHOT-12NL is a patient-reported questionnaire that measures health-related quality of life and physical function in younger, active patients with hip disorders. Scores on the iHOT-12NL range between 0 and 100 (worst - best possible function). This questionnaire will be filled out by the patient during admission and at 6 weeks, 3, 6 and 12 months follow up.

*Operation time*: the operation time is recorded in the surgical report.

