### Statistical analysis

Statistical analysis will be performed using SPSS (IBM Corp., Armonk, NY, USA). Primary analysis will be done according to the intention-to-treat principle. If patients are not treated according their allocated treatment a per-protocol analysis will be conducted to confirm the intention-to-treat analysis. Baseline characteristics of the treatment groups will be presented as mean with SD or as median and range for continuous variables and as number and percentage for categorical variables.

The primary outcome parameter, the incidence of revision surgery after 1 year, will be compared between the treatment groups using logistic regression analysis, including study centre as a covariate, since some study sites have used the DLBP for several years and whereas in other medical centres the DLBP has only been introduced recently. In literature there is no clear evidence of other covariates that have a strong or moderate association with the primary outcome. The secondary parameters: the incidence of AVN, non-union, implant-related complications, post-operative complications, and elective implant removal after 1 year will be analysed in the same manner as the primary outcome parameter. Operation time will be compared between the treatment groups using the independent samples t-test or the Mann-Whitney test, as appropriate. Functional outcome at the specified follow-up moments will be compared between the treatment groups using an independent samples t-test. In addition, the course of functional recovery over time will be compared using a linear mixed model with time, treatment and baseline characteristics as fixed effects, and patient as random effect. Missing data will be imputed using multiple imputation before testing the differences in the outcome parameters. *P*-values less than 0.05 will be considered statistically significant.

The economic evaluation will compare differences in societal costs, as described in the paragraph ‘Study parameters’, to differences in quality adjusted life years (QALYs). Utilities obtained from the EQ-5D-5L will be used to determine QALYs. The QALYs will be calculated from the area under the curve in a utility-time figure. The duration of the trial will be taken as the time-horizon. Group averages will be statistically compared using non-paired t-test and a net-benefit analysis will be used to compare costs to patient outcome. Results will be presented in a cost-effectiveness acceptability curve.

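### The mixed model for functional recovery lists no treatment-by-time term, and its random patient intercept would misstate the error of most contrasts such a term provides if correlation fades across visits

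*Protocol article*

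**What the plan says.** The iHOT-12NL is a secondary, patient-reported outcome on a 0 to 100 scale. On its timing, the protocol article (Secondary outcome parameters) states: "This questionnaire will be filled out by the patient during admission and at 6 weeks, 3, 6 and 12 months follow up". The post-operative visits are therefore unequally spaced, at 1.5, 3, 6 and 12 months.

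Statistical analysis plans two analyses of it. The first is visit by visit: "Functional outcome at the specified follow-up moments will be compared between the treatment groups using an independent samples t-test". The second is introduced with "In addition, the course of functional recovery over time will be compared", and the method is specified as "using a linear mixed model with time, treatment and baseline characteristics as fixed effects, and patient as random effect". No treatment-by-time term, random slope, residual covariance structure or robust standard error is named. On missing values the section says: "Missing data will be imputed using multiple imputation before testing the differences in the outcome parameters". The article gives no standard deviation for the iHOT-12NL and no correlation between visits.

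**The concern.** Two features of the model sentence work against its stated purpose.

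First, with time and treatment as separate fixed effects, the model describes two parallel recovery curves. The treatment coefficient is the average vertical distance between them. Whether the curves differ in shape or speed, which is what comparing the course means, is not tested by any listed term.

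Second, a single patient effect with independent residuals makes every pair of visits equally correlated and every visit equally variable. Scores 1.5 months apart (6 weeks and 3 months) would be as strongly correlated as scores 10.5 months apart (6 weeks and 12 months). During fracture recovery, with some patients healing and others failing, that is hard to defend. If correlation fades, the model applies one average correlation to all pairs. That average is too high for distant visits and too low for close ones, so treatment-by-time contrasts would get wrong standard errors and P-values.

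**Working it through.** The article states no figure for this model, so there is none to reproduce. The 121 patients per group from Sample size calculation enter only the simulation below, because the ratios do not depend on sample size.

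**Inputs.** From the article: visits at 1.5, 3, 6 and 12 months, two-sided 5% level. Assumed: correlation r per visit step of 0.6, 0.7 or 0.8, falling as r, r², r³; SD either constant or rising 16–20–24–26; complete data, which imputation would supply. These are covariances left after adjustment for baseline characteristics.

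**Method.** In balanced data the random-intercept model settles on the mean variance v and the mean between-visit covariance c of the true matrix S. For a between-arm contrast with visit weights w, let M be the matrix with v on the diagonal and c elsewhere. Then

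- SE ratio = √(w′Mw / w′Sw)
- actual type I error = 2Φ(−1.96 × SE ratio)

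**Worked case, r = 0.7, constant SD (variance set to 1).**

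- Mean correlation: (3×0.7 + 2×0.49 + 1×0.343)/6 = 3.423/6 = 0.5705.
- Time-averaged difference: model (4 + 12×0.5705)/16 = 0.678; true value the same. Ratio 1.000, type I error 5%.
- Change from 6 weeks to 12 months: model 2(1−0.5705) = 0.859; true 2(1−0.343) = 1.314. Ratio √(0.859/1.314) = 0.809, type I error 11.3%.
- Change from 6 weeks to 3 months: model 0.859; true 2(1−0.7) = 0.600. Ratio 1.197, type I error 1.9%.
- Slope in months (weights −4.125, −2.625, 0.375, 6.375; sum of squares 64.6875): model 64.6875×0.4295 = 27.78; true 45.86. Ratio 0.778, type I error 12.7%.

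**All assumed settings (SE ratio / type I error; type I error only for the joint test).**

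| r per step | SD | 6 wk to 12 mo change | Slope in months | 6 wk to 3 mo change | Joint 3-df treatment-by-visit |
|---|---|---|---|---|---|
| 0.6 | constant | 0.833 / 0.103 | 0.801 / 0.116 | 1.166 / 0.022 | 0.060 |
| 0.7 | constant | 0.809 / 0.113 | 0.778 / 0.127 | 1.197 / 0.019 | 0.063 |
| 0.8 | constant | 0.786 / 0.124 | 0.758 / 0.137 | 1.227 / 0.016 | 0.066 |
| 0.6 | rising | 0.840 / 0.100 | 0.774 / 0.129 | 1.397 / 0.006 | 0.062 |
| 0.7 | rising | 0.812 / 0.111 | 0.753 / 0.140 | 1.432 / 0.005 | 0.065 |
| 0.8 | rising | 0.783 / 0.125 | 0.732 / 0.151 | 1.468 / 0.004 | 0.068 |

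The time-averaged difference has ratio 1.000 in every row.

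**Checks.**

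- A simulation with 121 per arm, r = 0.7, constant SD and 40,000 replicates rejected in 5.0% (time-averaged), 12.5% (slope), 11.0% (6 weeks to 12 months) and 1.8% (6 weeks to 3 months).
- With r from 0.5 to 0.9 per step, or exponential decay of 0.90 to 0.97 per month, type I error is 9–14% for the long change, 10.5–17.5% for the slope and 5.7–7.4% for the joint test.
- With milder fading (monthly decay plus 20% measurement noise, with or without a permanent patient component) it is 7.1–9.3% for the long change and 8.1–11.7% for the slope.
- With constant correlation (0.6) and constant variance, every contrast is at 5%.

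**The case against.** The strongest objection is that the inflated error rates belong to terms the plan does not list. The one listed treatment term is correctly sized, so the model as written has no anti-conservative treatment test. This stands. It is why the missing treatment-by-time term comes first, and why the covariance matters only once that term is in.

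A reader might also infer that the recovery comparison is anti-conservative throughout. The figures do not support that. Errors for the change from 6 weeks to 3 months are too large, and the joint test, the natural one with visit as a category, is only slightly inflated. If spread also grows over time, the model's single-visit contrasts would be off too (about 10% at 12 months and 0.75% at 6 weeks with the rising SDs above). But the plan takes its per-visit comparisons from t-tests, which do not use this covariance.

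A third inference would be that the article rules out any other covariance. It does not say intercept only or independent residuals, SPSS accepts a residual structure beside a random effect, and a condensed article may leave that detail to a fuller document. This stands in part. Still, the article lists the model's terms rather than deferring them, and an analyst following the sentence would fit a random intercept.

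Finally, the size rests on correlations that the article does not give. That is correct, and the range is shown for that reason.

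**Conclusion.** The point holds in a limited form. As listed, the model cannot compare the course of recovery between implants. Adding the contrast that would do so, while keeping a plain random intercept, gives standard errors wrong in both directions if correlation fades. For correlations of 0.6–0.8 per visit step, standard errors are about 16–22% too small for the change from 6 weeks to 12 months and about 20–27% too small for the slope. For the change from 6 weeks to 3 months they are about 17–47% too large.

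The size rests on the assumed correlations and SDs and on balanced data; it is zero if variance and correlation are constant. It does not support a claim that the trial's functional results as a whole are biased towards false positives. The affected analysis supplements a secondary outcome, and the primary comparison of revision surgery does not depend on it. The change is worth making before the data are analysed because it is cheap.

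**What to change.** Restate the model as categorical visit, treatment, treatment-by-visit and the baseline covariates as fixed effects. Replace the random patient intercept with an unstructured within-patient covariance over the four post-operative visits, with the admission score kept out of the outcome vector. Name the treatment-by-visit contrast or joint test that will be read as the comparison of recovery course. State in advance a fallback if the model does not converge, such as heterogeneous first-order autoregressive, noting that it lets correlation fall per visit step rather than per month.

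Cost: an unstructured 4×4 matrix has 4×5/2 = 10 covariance parameters in place of two, so eight more. That is manageable with 266 planned patients and available in the repeated-measures part of the SPSS mixed procedure. The treatment-by-visit term adds three fixed-effect parameters. No new data are needed. The downside is the possible need for the convergence fallback. If correlation proves constant, almost nothing is lost.

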### Sample size calculation

The failure rate or revision rate of the DHS in patients ≤65 years with displaced FNFs described in today’s literature is 32–44% [8, 17]. The failure rate of the DLBP in patients of 60 years and younger with a displaced FNF in a previous cohort study was 13.2% [14]. Analysis of our data showed a failure rate of 15% for the DLBP in patients of 65 years and younger (non-published data). For the determination of the sample size we assumed a 30% failure rate for the DHS and 15% failure rate for the DLBP. For a power of 80% we need 121 patients per group to prove the superiority of the DLBP regarding the primary outcome (need for revision surgery) with alpha of 5% in a two-sided test. Taking into account that up to 10% of the patients may be lost to follow up, 266 patients need to be included for adequate statistical power, i.e. 133 patients per group.

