### Study procedures

A time schedule of procedures and measurements is presented in Table 1. The selection of eligible patients will take place in the emergency department (ED). According to standard care, X-ray examinations of the pelvis and hip are made on admission and assessed by the radiologist and trauma surgeon. Eligible patients will receive oral and written information about the study from the physician in the ED. The patients have at least 6 h to consider participation in the study and will be given the opportunity to ask questions about the study. Written informed consent will be obtained by the surgical resident or the surgeon after admission to the ward. Randomization will be done by the treating surgeon. After inclusion the patient will be allocated to one of the two study groups (DLBP or DHS) using an online randomization program. The baseline parameters will be registered by a nurse upon arrival on the surgical ward before surgery. The perioperative care will be the same for all included patients.

**Table 1 Tab1:** Time schedule for study procedures and measurements

	Emergency department	Admission	Post-op visit (≤5 days)	6 weeks follow-up	3 months follow-up	6 months follow-up	12 months follow-up	24 months follow-up^a^
Informed consent		x						
Baseline characteristics		x						
Radiography	x		x	x	x		x	
Questionnaires		x		x	x	x	x	x
Complications registration		x	x	x	x		x	x

^a^ Contact by telephone

Surgery will be performed by an (orthopaedic) trauma surgeon or by an (orthopaedic) trauma resident under the direct supervision of an (orthopaedic) trauma surgeon. The aim is to operate within 24–36 h based on the Dutch guidelines for treatment of FNFs [18]. After surgery, details about the surgery will be documented.

After discharge patients are scheduled for outpatient visits after 6 weeks, 3 and 12 months. Conventional radiographs will be taken and assessed during these visits (Table 1). The patients need to fill out a questionnaire before follow up visits and 6 months after discharge. Also, the patient will be contacted by telephone 24 months after enrolment in the study for additional questionnaires about mobility and complication registration.

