### Study parameters

#### Primary outcome parameter

The primary outcome is the incidence of revision surgery after fixation of an initially displaced FNF treated with DLBP or DHS due to non-union, AVN or cut out of the implant. This will be monitored during 1 year of follow up after surgery.

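### Imputation of 1-year revision status should condition on being unrevised at last contact; as written, nothing uses the event-free time of patients lost during the year

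*Protocol article*

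**What the plan says.** Under Primary outcome parameter, the protocol article defines the endpoint as revision surgery for non-union, AVN or cut-out, and adds: "This will be monitored during 1 year of follow up after surgery". The Statistical analysis section then fixes a yes/no comparison: "The primary outcome parameter, the incidence of revision surgery after 1 year, will be compared between the treatment groups using logistic regression analysis", with study centre as covariate. On incomplete data it has one sentence: "Missing data will be imputed using multiple imputation before testing the differences in the outcome parameters". It does not say which variables enter the imputation, and it plans no time-to-event analysis of revision. The same section finds no clear evidence of other covariates with a strong or moderate association with the primary outcome.

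The Sample size calculation section allows for loss: "Taking into account that up to 10% of the patients may be lost to follow up". Under Study procedures, "After discharge patients are scheduled for outpatient visits after 6 weeks, 3 and 12 months". Questionnaires are also due at 6 months, and a telephone contact at 24 months includes registration of complications.

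**The concern.** A patient who is revised and then lost has a known outcome. A patient who is lost first has an unknown outcome, but is known to have passed part of the year without revision. Missingness therefore depends on event-free status, and a plain 1-year yes/no variable does not carry that information.

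If the status is imputed from arm, centre and baseline data, lost patients are drawn at about the rate of the patients with known outcome. That pool keeps every revision that occurred before loss but has lost some of the non-events, so its rate is too high. Since the article expects little from other baseline covariates, these would do little to correct it.

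At stake are the revision rate in each arm, which will be the headline result, and, if loss differs between arms, the implant comparison itself. The trial is unblinded, so unequal loss is possible, although nothing in the article predicts it.

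**Working it through.** **Inputs from the article.** "we assumed a 30% failure rate for the DHS and 15% failure rate for the DLBP"; two-sided alpha 5%; "For a power of 80% we need 121 patients per group"; loss up to 10%.

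**The plan's own figure.** Two proportions, pooled variance, no continuity correction:

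n = [1.96·√(2·0.225·0.775) + 0.8416·√(0.30·0.70 + 0.15·0.85)]² / 0.15² = (1.1575 + 0.4889)² / 0.0225 = 120.5, so 121 per group.

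121 × 1.1 = 133.1, so 133 per group and 266 in total. The sample size is reproduced and is not affected by this point.

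**Assumptions not in the article.** Revisions and losses are spread evenly over the year, loss is unrelated to revision, and imputation uses only arm, centre and baseline. Let p be the true 1-year risk and L the share whose follow-up stops early.

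- Known revisions: p(1 − L/2)
- Known non-revisions: (1 − p)(1 − L)
- Missing: L(1 − p/2)
- Rate given to the missing, and so the rate reported: known revisions / (known revisions + known non-revisions)

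At L = 10%:

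- DHS: 0.285 / (0.285 + 0.630) = 0.31148, so 31.1% instead of 30%
- DLBP: 0.1425 / (0.1425 + 0.765) = 0.15702, so 15.7% instead of 15%

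The true remaining risk of the missing patients is (p/2)/(1 − p/2): 0.15/0.85 = 17.6% for the DHS and 0.075/0.925 = 8.1% for the DLBP. Using those values restores the truth; for the DHS, 0.285 + 0.085 × 0.1765 = 0.300.

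| Loss DHS / DLBP | DHS | DLBP | Difference (true 15.0 points) | OR (true 0.412) |
|---|---|---|---|---|
| 10% / 10% | 31.1% | 15.7% | 15.4 | 0.412 |
| 15% / 5% | 31.8% | 15.3% | 16.5 | 0.388 |
| 5% / 15% | 30.5% | 16.1% | 14.4 | 0.437 |

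The odds in each arm are [p/(1 − p)]·(1 − L/2)/(1 − L). With the same L in both arms the second factor cancels, so the odds ratio is exactly unchanged: (0.1425/0.765)/(0.285/0.630) = 0.412. With unequal loss it does not cancel: (0.14625/0.8075)/(0.2775/0.595) = 0.388 and (0.13875/0.7225)/(0.2925/0.665) = 0.437.

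**No true difference.** At 30% in both arms, loss of 15% against 5% gives 31.8% and 30.5%, a false gap of about 1.3 points.

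**Other timings.** Let G be the share of the year's revisions due by the time of loss and m the share actually missing. The remaining risk is r = p(1 − G)/(1 − pG), and the reported rate is (p − m·r)/(1 − m).

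- Loss right after surgery (G = 0): no bias.
- Early revisions, loss at 6 months (G = 0.75), m = 10%: for the DHS, r = 0.075/0.775 = 9.7% and the rate is (0.30 − 0.0097)/0.9 = 32.3%, 2.3 points too high. For the DLBP, r = 0.0375/0.8875 = 4.2% and the rate is 16.2%, 1.2 points too high.
- Over all timings tried with m = 10% in both arms, the difference lies between 15.0 and 16.1 points and the OR between 0.406 and 0.412.
- With m = 15% DHS and 5% DLBP, the difference lies between 15.0 and 18.0 points; reversed, between 14.2 and 15.0.
- With both arms at 22.5%, even timing and m = 15% against 5%, the false gap is 1.2 points and the type I error about 5.6%.

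**Precision.** In 20,000 simulated trials of 133 per arm (10% loss, even timing), the standard deviation of the difference was 0.0537 with known outcomes only and 0.0521 with Kaplan-Meier, about 3% larger.

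**The case against.** The strongest reply is that the article does not fix the defect. A reader might infer from the missing-data sentence that lost patients will be given the full-year risk. The text does not say so. It names no imputation model, and one that uses status at last contact, the interim radiographs and the questionnaires would fit its wording and would reduce or remove the bias. Imputation variables are also commonly left to the analysis plan or full protocol, which are not shown. This stands, and the point is therefore conditional. What remains is that the usual imputation of a yes/no variable does not take account of event-free time unless it is set up to do so, and nothing else in the stated analysis does.

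A reader might also infer that the rates must be biased upward. That needs loss to be unrelated to later revision. If patients leave because they are doing badly or are revised elsewhere, the sign can turn. In the even-timing DHS example it turns once their remaining risk exceeds the 31.1% they would be given, against 17.6% under unrelated loss. Kaplan-Meier would then understate the risk as well.

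Third, timing and unequal loss are assumptions. Clinic visits at 6 weeks, 3 and 12 months make even loss doubtful, and non-union is generally judged at 9 months or later unless revision comes sooner, so revisions may fall late. If all loss follows the 3-month visit and 15% of revisions have occurred by then, 10% loss gives 0.2745/0.9045 = 30.3% and 0.13725/0.90225 = 15.2%, a difference of 15.1 points. The 24-month call may also recover outcomes, and a recovered outcome is not missing. All this limits the size but does not remove the mechanism.

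**Conclusion.** The point holds in a limited, conditional form. As worded, the plan joins a yes/no outcome to multiple imputation for an event that accrues over the year, and does not say that event-free time is used. If it is not used and loss is unrelated to later revision, the per-arm rates are overstated by about 1.1 points (DHS) and 0.7 points (DLBP) at 10% loss with even timing, and by 0 to 2.3 points across the other timings and both arms.

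The implant comparison is nearly untouched when loss is equal. The planned odds ratio is then unchanged or almost so. The difference moves by about 1.5 or 0.6 points, according to direction, only if loss is as uneven as 15% against 5%, for which the article gives no evidence. The documents do not support a claim that the comparison is seriously biased or that the trial is underpowered for this reason. This is a cheap improvement to the analysis wording.

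**What to change.** Keep the centre-adjusted logistic model and add a sentence on the primary outcome. A patient lost before 12 months has the outcome imputed from patients of the same arm who were still unrevised at that contact, with the interim radiographs, iHOT-12NL and EQ-5D-5L as auxiliary variables. Outcomes learnt at the 24-month call are used as observed. Alternatively, and at least as a sensitivity analysis, estimate the 1-year revision risk per arm by Kaplan-Meier from the revision date or last event-free contact, with centre as stratum. If the analysis plan already does one of these, a cross-reference is enough.

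The cost is a little more programming and, probably, slightly lower reported revision rates. Dates of revision and of last contact must be captured; the article does not say that they are, so the data capture should be checked. Both options still assume that loss is unrelated to later revision given arm, centre and event-free time (and, for the imputation, the auxiliary variables). Design and sample size do not change.
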